## Case incidence cohort

The sample size calculations for the case incidence cohort were calculated using the formula for cluster randomized trial event rates with a person-time denominator [5]. Assumptions utilized in the calculations are summarized below. These assumptions are based on data from similar studies conducted in comparable settings for each study site. In each case, the calculation was completed for the person-time required to demonstrate superiority with a 30% reduction in cumulative clinical case incidence of malaria over a 2-year period. Note that cohort follow-up time differs across the sites. A seasonal cohort will be implemented in Mali (8 months of follow-up per study year) and Zambia (6 months of follow-up per study year). In Kenya, the cohort study will run continuously for the 2-year period,however, the cohort will be rotated every 6 months (i.e., each individual will be followed for up to 6 months) in the first year but will not be rotated (e.g., each individual will be followed for 1 year in the second year).

## Cross-sectional household survey

The sample size calculations for the parasite prevalence surveys were calculated using the formula for cluster randomized trial proportions [5] using PASS 15 Sample Size Software (©NCSS, Kaysville, Utah) for Kenya and Zambia, and R (© The R Foundation) for Mali.

### Passive case detection

Data from all health facilities regarding people of all ages will be used to calculate confirmed malaria case incidence in the intervention and control clusters in Mali and Kenya. In Kenya, specific dates for data collection will be specified in the study site-specific SAP and protocol in terms of timing of data collection/analysis start after ATSB deployment (i.e., a wash-in period of ~ 2 weeks after ATSB deployment may be included and should be precisely pre-specified in Kenya site specific SAP). In Mali, facility-based assistants use electronic tablets with a custom application for collecting case data. Data will be transmitted weekly to the field data manager. In Kenya, health care data are entered into ScanForm (https://about.scanform.qed.ai/) registers at facilities and by community health workers. Individually identifiable data will not be extracted or collected by the trial staff for this outcome.

### Entomological endpoints

Entomological monitoring will be conducted monthly in a sub-set of clusters throughout the course of the trials. While a number of secondary endpoints will be based on these collections, power and sample size calculations in terms of the number of entomology clusters, number of participating households, and number of nights of collections were based specifically on parity status of female mosquitoes, which is a proxy for the daily female vector mosquito survival. Sample size calculations/power analyses were carried out separately for each trial site and are presented as follows. The power to detect the effect of the ATSB intervention on the non-parous rate (NPR) was estimated by analysis of 1000 simulated trial data sets. The effect of the intervention was assumed to be a reduction of daily survival probability from 80% in the control arm to 75% in the intervention arm, equivalent to an increase in NPR from 48.8 to 57.8% based on the formula from Davidson (Davidson, 1954). Each data set was simulated from a generalized linear mixed-effects model (GLMM) with a binomial response, which was the number of non-parous females counted out of the total number of females collected. Variation in NPR between clusters, households, and months was simulated as normally distributed random effects on the logit scale. The household random effect variance of 0.18 was estimated from pilot data collected in Mali. The cluster random effect was estimated from the same data, but the upper 50% confidence limit of 0.04 was used in preference to anti-conservatively using the point estimate of zero. The inter-month variance was set at 1, giving a monthly mean NPR range of approximately 0.2 to 0.8. The total number of female mosquitoes trapped per household per night was sampled from a simulated Poisson distribution with a mean catch of 2.5 females. Inter-cluster and inter-month variation in the number trapped was simulated as normal random effects on the log scale with variances of 0.16 (equivalent to a coefficient of variation of 0.4) and 0.5 (giving a monthly mean catch range of approximately 0.5 to 6) respectively. The number of clusters to be included per arm of the study to achieve at least 80% power with a 0.05 two-tailed alpha is shown in the table below (along with several other assumptions).

### Framework

The trials are planned under a superiority framework. The comparisons will consist of two-sided tests of the null hypothesis of no difference in efficacy between the ATSB (intervention) arm and the control arm. All primary comparisons will consist of comparisons of the outcome in the intervention arm vs. the outcome in the control arm.

### Statistical interim analyses and guidance

One interim analysis is planned in Mali and Zambia. In Kenya, an additional (second) interim analysis is planned because this trial has a 6-month-longer follow-up than the other two trials because transmission occurs throughout the year in Kenya. In Kenya, the interim analyses will be event, rather than time, driven. In Mali and Zambia, the interim analysis will be conducted at the end of the first transmission season in the first year.

In Kenya, interim analyses will occur either after 50% and 75% of person-time have been completed (i.e., after about 1 and 1.5 years respectively), or after 50% (*n* = 415) and 75% (*n* = 622) of the total number of expected primary outcome events over 2 years in the control arm (*n* = 829) have occurred (whichever comes first). The number of events will be tracked by an independent statistician. In Zambia and Mali, an interim analysis will be conducted after the first transmission season regardless of the total number of events.

The interim analysis will consider a stringent rule in each site based on the Haybittle-Peto boundaries to preserve the overall two-sided type I error rate for efficacy at the *α* = 0.05 level at the final analysis. As such, each interim analysis will use an *α* = 0.001 thereby reducing the probability of type-I error to less than 1 per 1000. The final null-hypothesis significance testing will be conducted with standard alpha levels of 0.05 because of the stringent type-I error criteria proposed for the interim analyses. Because of the stringent* α* levels applied and the smaller sample sizes expected at interim analysis, the power to detect the effect is expected to be low, meaning that a positive interim result is only expected in the case in which the effect size is much larger than expected, variance in outcome data is low, the incidence of disease in the reference arm is much higher than anticipated, or a combination of these factors occurs.

Each study site DSMB will be responsible for determining when an interim analysis is required per trial rules which is automatic in Mali and Zambia at the end of year one. If an interim analysis is indicated, an independent statistician will, in collaboration with the DSMB, conduct formal tests of the study data against the following rules:

Firstly, the trial statistician will provide the independent statistician and DSMB with a dataset prepared for analysis with a dummy treatment code. The independent statistician and DSMB statistician would replace the dummy random treatment code with the actual allocation code and conduct the analysis. Finally, after reviewing the analysis output and verifying the results, the independent statistician in collaboration with the DSMB would summarize the findings in a report addressed to the other members of the DSMB.

### Overwhelming benefit rule

The DSMBs of each trial may consider recommending an early submission of the ATSB dossier for overwhelming benefit if a test of the null hypothesis that the cumulative clinical incidence of malaria in the intervention arm in the intention to treat analysis population is lower than the cumulative clinical incidence in the intention to treat analysis population of the control arm. The null hypothesis was equal incidence between the two arms; the interim analysis assumes a two-sided test of the null hypothesis at a significance level of *α* < 0.001. This test will be conducted using a variance component regression model with a Poisson likelihood and a log link function which includes random cluster-level intercepts. The regression will include a fixed effect for study arm, and the hypothesis will be tested by testing that the incidence rate ratio associated with this covariate is not significantly different than 1 with a *p*-value < 0.001. The DSMB has been tasked with only making a recommendation about early referral of the trials to the vector control advisory group (VCAG) at the World Health Organization. This recommendation is only expected after the results of two trials show significant benefit, either in the interim or in the final analysis. As such the independent statistician working in collaboration with each trial site will advise the DSMB of each trial site on the results of the interim analysis as well as results of interim or final analyses of the other trials. The DSMB can thus include the interim results from other sites in their consideration of recommending an early referral to the VCAG.

A DSMB recommendation to discontinue the trial will not be based on the results of this statistical test. The DSMB can advise continuing the trial even if statistically the boundary is crossed, e.g., in order to continue collecting more epidemiological, entomological, or safety information or data for further sub-group analyses. It is the intent of the investigators to continue the trial even in the case of an early efficacy demonstration across more than one site since there is an expectation of significant heterogeneity in the effect of ATSB across entomological settings.

### Stopping for harm

The trials do not include formal stopping rules based on harm, because the intervention is not targeted to humans and the expected risk to trial participants is expected to be minimal; thus, formal harm-based stopping rules are not needed. However, this does not preclude the DSMB from stopping the trial for harm should unforeseen consequences of the ATSB or trial procedures lead to harm. For example, deliberate abuse or misuse of the ATSB products or unforeseen non-target insect impacts could lead to harm which causes trial stoppage.

### Timing of final analysis

Should no early stopping rule be invoked and the trials continued after each interim analysis, then the final analysis per trial (country) will be conducted collectively at the end of two seasons/years. This analysis will occur at the site (trial) level. A final pooled individual participant data (IPD) analysis and meta-analysis of trial outcomes will be conducted collectively after the termination of the trials in all sites.

## Timing of outcome assessments

### Primary and secondary efficacy outcomes

#### Primary outcome

The primary outcome measure is the incidence rate of clinical malaria defined as history of fever or a measured temperature ≥ 37.5 °C and a positive malaria rapid diagnostic test (RDT) (the definition is specified in full in a later section). This will be assessed among people aged 12 months to less than 15 years (≥ 5 to 15 years in Mali). These outcomes will be ascertained through follow-up visits. Visits will be conducted within ± 5 days for true monthly intervals and specific follow-up time between visits will be computed to the nearest one day.

#### Secondary outcomes

Prevalence of malaria infection among participants aged 6 months and older, detected by RDT. This outcome will be assessed annually cross-sectionally (or through a rolling prevalence survey in Kenya). For the cross-sectional analyses (Zambia, Mali), measurement will occur in each member of the study sample within an approximate 1-month (30-day) observation window.Incidence rate of passively reported clinical malaria among participants of all ages, defined as the number of malaria confirmed cases (by RDT or microscopy), linked to study clusters by place of residence, per 1000 population per year, using routine data from health facilities serving the study population (e.g., by name of village of residence) and cluster population sizes for the denominator. This outcome is assessed daily at routine health facilities and dispensaries (Mali and Kenya only).Parity as a proxy for daily female vector mosquito survival—this outcome is defined as the non-parous proportion, e.g., the proportion of freshly-caught, non-blood-fed female adult *Anopheles* spp. mosquitoes captured during Human Landing Catches which have never been gravid as determined by the method of Detinova. The outcome is assessed in a sub-sample of clusters, houses, and nights on a monthly basis.Mosquito abundance—The number of adult *Anopheles* spp. captured in CDC UV Light traps.Sporozoite rate—The number of adult female *Anopheles* spp*.* captured via HLC or CDC UV light traps found to be sporozoite positive by anti-circumsporozoite protein (α-CSP) enzyme-linked immune-sorbent assay (ELISA) divided by the number of adult female *Anopheles* spp. tested in ELISA assay.Human landing/biting rate—The number of adult female *Anopheles* spp. captured via HLC divided by the number of person-nights (days) of HLC collection.Entomological inoculation rate—The human landing/biting rate (6) multiplied by the sporozoite rate (5) multiplied by 365 days per year to yield annualized EIR. It should be noted that all EIR estimates will be expressed in terms of annual rates.

## Statistical principles

### Confidence intervals and *p*-values

The trial is generally intended to control type-I error to less than 5%. As such, given the planned interim analyses at each trial site, type-I error will be controlled using an Haybittle-Peto boundaries as discussed above. The main trial results (treatment efficacy estimates) will be presented with 95% confidence intervals and two-sided *p*-values.

### Adherence and protocol deviations

Since the intervention is deployed on a group basis rather than individually, adherence definitions will take account of this. Standard adherence will be defined as the intention to treat a cluster of residences with ATSBs, as randomized. Individual adherence will be defined based on ATSBs present at individuals’ households. Both individual and cluster-level adherence measures will be defined and pre-categorized prior to final analysis and used to categorize the per-protocol trial population.

The per-protocol analysis populations will be defined as those living in intervention clusters where ATSB was deployed and replaced according to the planned schedule. Clusters where more than 1-month delay in ATSB deployment occurred or where substantial deployment of ATSB into control areas occurs (e.g., deployment consistent with distribution of ATSB to control areas) will be removed from the per-protocol analysis population.

Standard protocol deviations will be considered reportable/summarizable when clusters refuse placement of ATSB or have been treated/not treated contrary to their randomization assignment and providing initial study consent. Additionally, protocol deviations will be considered to have occurred if ATSB replacement visits for an entire cluster by the study team are delayed by more than 3 weeks from the expected timeline according to study planning.

Protocol deviations related to failure to deliver or replace ATSB will be summarized in the final trial reports as well as incorporated into the calculation of adherence.

### Analysis populations

There are two analysis populations for the primary outcome assessment: These are the intention-to-treat population and the per-protocol analysis population. The intention-to-treat population consists of all eligible individuals recruited and consented to participate in the study. The primary analysis will be conducted on the intention-to-treat population. Per-protocol analysis populations will be those eligible, recruited, and consented individuals whose adherence at cluster level meets the adherence standard. Additional household-level per-protocol analysis may be conducted consisting of ATSB deployment at the household level consistent with randomization assignment.

### Multiplicity

While the trial tests multiple secondary outcomes, no adjustment will be made for multiplicity because the trials each have two arms and a single primary outcome. Additionally, each trial is powered and run independently and as such no adjustment for multiplicity on account of the three trials is being made. Secondary outcomes are assumed to be on the same causal pathway as the primary outcome and as such are also not adjusted for multiplicity of testing since these are expected to relate to the same hypothesis.

### Trial population

The trial population, as a whole, consists of all de facto and *de jure* residents present in intervention and control clusters (and associated buffer areas where applicable) during the study period. The population to be sampled for outcome assessment considers several additional criteria for inclusion in the cohort studies as outlined below. The clusters for the trials are circumscribed geographic areas usually representing from one to a few villages or in some cases in Zambia, geographically identified parts of villages. Clusters generally represent somewhere from 100 to 400 households in size and widely vary in geographic area. Individuals greater than 18 years of age will provide individual consent. For individuals aged 6 months to less than 18 years of age, consent will be sought from the parent or guardian of the child. For children greater than 6 years and less than 18, oral assent will be sought from the child.

### Screening data

Since the trial is conducted as a cluster randomized study, no individual screening is conducted. Trial areas will be enumerated prior to cohort enrollment and the enumeration will identify households with residents that meet eligibility criteria for cohort participation and for eligibility in cross-sectional household samples (e.g., eligible aged children for outcome assessment). Cluster-level screening is anticipated to be conducted during a baseline period in each study site. A larger number of clusters than planned for the final study power will be included in each site (~ 10% extra clusters). These clusters will be included in baseline data collection but excess clusters will be excluded prior to randomization. Exclusion will consider the following criteria: malaria prevalence and incidence defined as per primary and secondary trial outcomes with a specific aim to exclude any clusters found to have zero or near zero malaria incidence or prevalence in the baseline period or those with dramatically higher incidence/prevalence as compared to other study clusters (e.g., incidence or prevalence > three standard deviations from the mean incidence or prevalence of all baseline clusters will be considered for removal from the study if excess clusters remain after removal of clusters with zero or near zero incidence and prevalence). Additionally, logistical feasibility of implementation will also be considered with clusters in which implementation of intervention or data collection is determined to be impracticable, to be considered for exclusion, or where community-level consent for participation in the trial is refused.

### Eligibility

Eligibility for participation is described in detail in the protocol but in short, the cohort monitoring requires that the individual resides in the study areas within the core sampling areas and additionally is a:Household residentAt least 12 months of age and less than 15 years of age at the time of enrollment (≥ 5 to 15 in Mali, to exclude those covered by Seasonal Malaria Chemoprevention).

And is not a:Resident whose home is located within a buffer zonePregnant at the time of cohort enrollment.Pregnant at any time during the cohort study.

### Recruitment

Recruitment into the cohort study will be conducted by first completing an enumeration of all households and their members in the study clusters. This enumeration will be used as a sampling frame to select households with eligible individuals for the cohort study. Within each study cluster, a simple random sample of households with eligible individuals will be selected. In Mali and Kenya, a simple random sample of individuals will be selected from census lists. Within clusters, sampling for the cohort study will exclude people living in households within a geographic buffer zone around the perimeter of the cluster. Further details of recruitment are contained in the master trial protocol.

The CONSORT diagram will include at minimum the following elements shown in Table 5.

**Table 5 Tab5:** CONSORT diagram contents

Cohort study (For each cohort)	Cross-sectional study (each round)
Number of study clusters (by arm)	Number of Study clusters (by arm)
Number of sampled houses (by arm)	Number of Sampled houses (by arm)
Number of consented participants (HHs with participants) (by arm)	Number of consenting houses (by arm)
Number of participants (HHs) randomized to each study arm	Number of completed interviews (by arm)
Number of monthly follow-up visits conducted (by arm)	Number of tested individuals (by arm)
Number of missing HH monthly visits (by arm)	Number of Incomplete HH surveys (by arm)
Number of participants (HH) lost completely to follow-up (by arm)	Number of identified eligible participants not tested (by arm)
Number of participants (HH) completing (by arm)	

### Withdrawal/follow-up

It is anticipated that there will be approximately 20% LTFU withdrawal from each cohort. This is accounted for in the sample size calculations. Level of non-participation in the cross-sectional household surveys is expected to be 10–20%. LTFU will be summarized by arm and by cluster.

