### Sample size

Full details of the sample size calculations are contained in the trial master protocol and study site-specific protocols; the sample size determination is presented here in summary form (Tables 2, 3, and 4).

**Table 2 Tab2:** Sample size for incidence

	Mali	Kenya	Zambia
Clusters per arm (overall)	38 (76)	35 (70)	35 (70)
Trial duration in calendar years (seasonality of FU) (total FU per participant time in months)	2 years (8-month seasons) (16 months FU)	2 years (12-month seasons) (24 months FU)	2 years (6-month seasons) (12 months FU)
α (type 1 error probability for 2-year trial)	0.05 (Haybittle-Peto with one interim analysis)	0.05 (Haybittle-Peto with two interim analyses at approx. 50% and 75%)	0.05 (Haybittle-Peto with one interim analysis)
Power	88%	80%	80%
Baseline incidence of clinical malaria in the target age group	0.40 events per person-year (based on 0.6 incident events during an 8-month malaria season) (5y– < 15y)	0.845 events per person-year during a 12-m malaria transmission season (1y– < 15y)	0.50 events per 6-month malaria season (Jan–Jun) (1y– < 15y)
Reduction in baseline incidence (incidence rate ratio = 0.70)	30%	30%	30%
Coefficient of variation	0.40	0.40	0.40
Assumed loss of person time, including true LTFU plus loss due to exclusion of person time following each treatment with AL	20%	20%	34%
Total person-years required (number enrolled per cluster before loss-to-follow-up)	3850 person-years (obtained by enrolling 38 individuals per cluster to account for loss-to-follow-up, followed for a total of 16 months)	1260 person-years (obtained by enrolling 13.5 individuals per cluster to account for loss-to-follow-up, followed for a total of 24 months)	1610 person-years (obtained by enrolling 35 individuals per cluster to account for loss-to-follow-up, followed for a total of 12 months)

**Table 3 Tab3:** Sample size for prevalence outcomes

	**Mali**	**Kenya**	**Zambia**
Cluster per arm	38	35	35
α (2-tailed)	0.05	0.05	0.05
Power	90%	80%	90%
Baseline parasite prevalence measured by RDT among participants aged 6 months and older	50%	29.0%^a^	50.0%
Reduction in baseline prevalence	30%	30%	30%
ICC = intracluster correlation coefficient (coefficient of variation)	0.16 (cv = 0.4)	0.05	0.10
Non-response	20%	20%	20%
Sample size per cluster (accounting for non-response)	25 (32)	24 (30)	16 (20)
Total sample size per survey round/year (accounting for non-response)	1900 (2432)	1680 (2100)^b^	1120 (1400)

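### Table 2's required person-years for Mali and Kenya do not follow from the stated clusters, enrolment, follow-up and 20% loss

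*SAP article*

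**What the plan says.** All references are to the SAP article.

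- Withdrawal/follow-up anticipates "approximately 20% LTFU withdrawal from each cohort. This is accounted for in the sample size calculations".
- Sample size, Table 2, has a row for a broader quantity: "Assumed loss of person time, including true LTFU plus loss due to exclusion of person time following each treatment with AL". It gives 20% for Mali, 20% for Kenya and 34% for Zambia.
- The last row of Table 2 is headed "Total person-years required (number enrolled per cluster before loss-to-follow-up"), so the person-years are what the trial needs and the enrolment is what is recruited before losses.
- Mali: "3850 person-years (obtained by enrolling 38 individuals per cluster to account for loss-to-follow-up, followed for a total of 16 months"), with 76 clusters and 88% power. The baseline rate is given as "0.40 events per person-year (based on 0.6 incident events during an 8-month malaria season").
- Kenya: "1260 person-years (obtained by enrolling 13.5 individuals per cluster to account for loss-to-follow-up, followed for a total of 24 months"), with 70 clusters, 0.845 events per person-year and 80% power.
- Zambia: "1610 person-years (obtained by enrolling 35 individuals per cluster to account for loss-to-follow-up, followed for a total of 12 months"), with 70 clusters and 80% power.
- Statistical interim analyses and guidance expects 829 primary events in Kenya's control arm over two years. It times the looks at 50% and 75% of person-time or of those events, whichever comes first.

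**The concern.** The last row of Table 2 should be a simple product: clusters, times number enrolled, times years followed, times the fraction of person-time kept. If it is not, the reader cannot tell whether a printed total is gross or net, or what loss the trial was planned to withstand.

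The three trials are presented as harmonised, so the row invites comparison across sites. In Kenya, total person-time is also one of the two scales that time the interim analyses. What is at stake is whether the stated sample-size figures are correct and can be compared. A shortage of participants is not the issue.

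**Working it through.** **Inputs.** Clusters, enrolment per cluster, follow-up, loss, rate ratio 0.70, coefficient of variation 0.40 and baseline rates are all from Table 2. The two-sided test is from Framework, with alpha 0.05.

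**Person-years.** Gross = clusters x enrolled per cluster x years. Net = gross x (1 - loss). Implied loss = 1 - printed/gross.

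| Site | Gross | Stated loss | Net at stated loss | Printed | Implied loss |
|---|---|---|---|---|---|
| Mali | 76 x 38 x 16/12 = 3851 | 20% | 3081 | 3850 | 0% |
| Kenya | 70 x 13.5 x 2 = 1890 | 20% | 1512 | 1260 | 33.3% |
| Zambia | 70 x 35 x 1 = 2450 | 34% | 1617 | 1610 | 34.3% |

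Zambia reproduces. Mali and Kenya do not, and inflating by (1 + loss) instead of dividing by (1 - loss) does not rescue them: 3851/1.2 = 3209 and 1890/1.2 = 1575.

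Read the other way, delivering the printed totals at 20% loss would take 3850/(76 x 16/12 x 0.8) = 47.5 per cluster in Mali (38 stated) and 1260/(70 x 2 x 0.8) = 11.25 in Kenya (13.5 stated).

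**Power.** Case incidence cohort names the cluster-randomised event-rate formula with a person-time denominator but does not print it. I used its standard form, with c clusters per arm, y person-years per cluster, k = 0.40 and λ1 = 0.70 λ0:

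power = Φ( √[ (c - 1)(λ0 - λ1)² / { (λ0 + λ1)/y + k²(λ0² + λ1²) } ] - 1.96 )

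- Mali, λ0 = 0.40, λ1 = 0.28, c - 1 = 37. At 3850, y = 50.66: √(0.5328/0.05157) - 1.96 = 1.25, power 89.5%. At 3081, y = 40.53: √(0.5328/0.05492) - 1.96 = 1.15, power 87.6%. Stated: 88%.
- Kenya, λ0 = 0.845, λ1 = 0.5915, c - 1 = 34. At 1260, y = 18: √(2.185/0.2500) - 1.96 = 1.00, power 84.0%. At 1512, y = 21.6: √(2.185/0.2367) - 1.96 = 1.08, power 85.9%. Stated: 80%. By this formula 80% needs only about 930 person-years in total.
- Zambia at 1610: 80.4% if 0.50 is entered as a rate per person-year, 87.9% if it is annualised to 1.0. Stated: 80%.

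**Mali's baseline rate.** An incidence of 0.6 per 8-month season annualises to 0.6/(8/12) = 0.90 per person-year; 0.40 is what 0.6 x 8/12 gives. At 0.90 the power is 92.8% at 3081 and 93.5% at 3850, so neither total then gives 88%.

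**Kenya's expected events.** Control-arm events = half the total person-years x 0.845, taking equal person-time by arm:

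- 1260 total: 630 x 0.845 = 532
- 1512 total: 756 x 0.845 = 639
- 1890 gross: 945 x 0.845 = 799

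The stated 829 would need 829/0.845 = 981 control-arm person-years, more than the gross 945.

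**Loss to follow-up against total loss.** If loss to follow-up alone is 20%, a total of 20% in Mali and Kenya leaves nothing for the two weeks removed after each treated case (Outcome definitions). In Kenya that removal is about 0.845 x 14/365.25 = 3.2% of person-time. Together the two give 1 - 0.80 x 0.968 = 22.6%, so the exclusion does not explain 33% either.

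**The case against.** The strongest reply is that this is a summary table, with full calculations left to the protocols, and that nothing important moves. On power that stands. Trial design promises at least 80% per trial, and every candidate total for Mali and Kenya exceeds it. Kenya's enrolment covers more loss than the table declares, so its discrepancy is on the safe side. The reply does not excuse printed figures that disagree within one column; that is not detail left to another document.

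Four stronger readings are tempting and are not supported:

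- A reader might infer that all three sites contradict the 20% in Withdrawal/follow-up. Zambia does not. Its 34% is openly defined as loss to follow-up plus post-treatment exclusion, and 20% of the former can sit inside it.
- A reader might infer that Mali's 3850 is certainly a gross figure printed in a net row. The stated 88% lies slightly nearer the power at 3081 than at 3850, but both are within two points, and the comparison depends on 0.40 per person-year, which conflicts with the seasonal figure in the same cell. It could equally be a true requirement that 38 per cluster does not deliver.
- A reader might use 1260 or 1512 to place Kenya's first look at 630 or 756 person-years. The interim section does not link its percentages to Table 2. It gives approximate calendar times and an event alternative, and its 829 events fit neither total.
- A reader might infer that Kenya's follow-up was really 20 months, since 70 x 13.5 x 20/12 x 0.8 = 1260. The table says 24 months, so this is only a possible origin of the number.

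**Conclusion.** The point holds for the Mali and Kenya columns of Table 2. Mali's total carries no loss where 20% is stated: 3850 against about 3080 is 25% too high if a net figure was meant. Kenya's implies 33% where 20% is stated: 1260 against 1512 is 17% lower. Kenya's 80% power is not what the named formula returns for either total.

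This is an error of stated figures. It does not show an underpowered trial. The power values assume the standard form of the formula, equal cluster sizes and Table 2's own rates. Which Mali figure and which Kenya loss were intended cannot be settled from the document.

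**What to change.** In Table 2, print gross and net person-years for each site with the loss actually used.

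- **Mali:** either label 3850 as gross with about 3080 net, or state that 3850 net is not delivered by 38 per cluster. Reconcile 0.40 per person-year with 0.6 per 8-month season and restate the power on the rate kept.
- **Kenya:** declare 20% loss (1512) or 33% (1260), and restate the power. Reconcile total person-time with the 829 expected control-arm events in the interim section.
- **Zambia:** no correction; show 2450 gross and 1617 net (printed as 1610) for comparability.
- **Withdrawal/follow-up:** say that 20% is loss to follow-up alone, and how this fits a 20% total loss in Mali and Kenya once post-treatment exclusion is counted.

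The cost is one restated table row, the related power and rate entries, and a few sentences. No extra enrolment is needed.
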